### Sample size calculation

The sample size is calculated on the primary outcome. Using data extracted from questions in the previous qualitative study, sample size for an unclustered study with a 5 % two sided Type 1 error and 80 % power to detect a 25 % difference in mean questionnaire score, would be 114 women in each arm. Both Daly et al. in USA and Srikanth et al. in India found a very low level of knowledge about causes and risk factors for otitis media in mothers of young children [37, 40]. We anticipate a similarly low level in Jumla, and hypothesise that a 25 % increase would be modest and achievable. The cluster sizes are set at the size of the women’s groups which is around 20 women. To adjust for clustering, it is necessary either to establish an approximate intra-cluster correlation coefficient (ICC) or ρ, which measures the similarity of individual responses within clusters, in order to calculate the design effect (the number by which an individual trial must be multiplied to adjust for clustering) or to calculate the between cluster variability, k. These values vary and any estimate can only be approximate. Other studies on neonatal mortality in women’s groups in Nepal have found a very low ICC of 0.00644 [24]. Tielsch et al. [41] calculated a design effect of 1.23 with their study of supplements to prevent malnutrition in children. Mullany et al. [22] used a design effect of 2.0 for their study looking for a 25 % reduction in omphalitis in newborns in rural Nepal. Slightly further afield in Bangladesh, Aboud et al. [23] calculated an ICC of 0.03 for a responsive feeding and stimulation intervention to clusters of rural women and children. Pagel et al. [42] reviewed ICC for interventions around perinatal outcomes in low resource countries and found universally low ICC for maternal and neonatal mortality but higher ICC for other interventions such as skilled birth attendance. For example, in India and Bangladesh skilled birth attendance ranged from ICC 0.02-0.04. The Design Effect (DEff) is the number by which the sample size for an individual randomised controlled trial must be multiplied to give the equivalent power to a cluster randomised trial. The Design Effect also considers the number of individuals in each cluster *– m.* Using the equation DEff = 1 + (*m*-1) ρ, assuming ρ = 0.03, would give a DEff = 1.6, or 182 women per arm. Using the safe equation DEff = 1 + (m-1) ρ, assuming ρ = 0.05, would give a DEff = 1.95, or 223 women per arm. This would translate into 11 clusters per arm. To account for stratifying, we have added a conservative extra two clusters per arm, which would make 13 clusters per arm. To enable robust cluster analysis a minimum of 15 clusters is ideal. This will provide a generous total sample of approximately 600 women in 30 clusters, 15 in the intervention and 15 in the control arm.

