
### Statistical analysis

Analysis will be by intention-to-treat, all study participants will be included in the analysis, even if lost to follow-up. Analysis will be adjusted for clustering. Every effort will be made to have complete data but missing data will not be ignored in the analysis. Data will be checked and cleaned before being entered into Statistical Package for the Social Sciences. At baseline a comparison profile of both intervention and control groups will be provided. The primary and secondary outcomes - difference in mean questionnaire score and prevalence of CSOM - will be compared between the two groups. Data will be analysed at both individual and cluster level. Cluster level analysis is very robust and, with 15 clusters in each arm, individual level analysis, adjusted for clustering ought also to be very robust. For the primary outcome, a summary measure, the mean score of the questionnaire, will be calculated and then the intervention and control group compared for significance with a *t*-test at the cluster level. For individual level analysis, we plan to use mixed effects linear regression, which adjusts for the effect of clustering. The secondary outcome is a proportion, so we plan to analyse individual level data using logistic regression random effects model, using quadrature checks, which also adjusts for clustering. Since the age range is quite broad we will consider each standard age grouping in our analysis: under one year, under five years, and five years and over. We will also analyse duration of ear discharge as this is strongly correlated with prognosis. Covariates including socioeconomic status, education, caste, geography and number of household members will be considered.

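### Two analyses of the primary questionnaire score are planned with an open covariate list and no deciding test, and neither is specified with the baseline score or the allocation strata

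*Protocol article*

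**What the plan says.** The Statistical analysis section of the protocol article states "Data will be analysed at both individual and cluster level". For the primary outcome it describes two analyses:

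- A t-test at cluster level on the mean questionnaire score. The reference to testing for significance is attached to this analysis.
- An individual-level model: "For individual level analysis, we plan to use mixed effects linear regression, which adjusts for the effect of clustering".

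On their standing it says "Cluster level analysis is very robust and, with 15 clusters in each arm, individual level analysis, adjusted for clustering ought also to be very robust". Neither is called primary, confirmatory or sensitivity, and no rule covers disagreement. The Abstract lists both without ranking them.

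The section ends by saying that covariates will be considered. It names five (socioeconomic status, education, caste, geography, household size) as examples, gives no selection rule and ties them to no particular model.

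The Sample size calculation section sets a single error rate: "5 % two sided Type 1 error and 80 % power to detect a 25 % difference in mean questionnaire score, would be 114 women" per arm.

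Under Study design and Outcome measures, the baseline questionnaire is completed before allocation, and allocation is stratified by geography. The analysis section gives the baseline score no role in estimating the effect.

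**The concern.** A single hypothesis was sized at a single 5% two-sided error. With two tests of it, one of them with or without covariates, a significant result can be picked from several correlated p-values, and the error rate then depends on how that choice is made. If the two analyses fall on opposite sides of 0.05, the article gives no way to decide what the trial found.

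The second issue is efficiency. The baseline score is measured before allocation and is a natural predictor of the follow-up score. The strata restrict the allocation. A plain two-sample t-test uses neither. It leaves any between-stratum variation in the error term, which costs power if the strata are prognostic.

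**Working it through.** **1. The plan's own figures.** Inputs from Sample size calculation: 114 women per arm unclustered, about 20 women per cluster, ICC 0.05 or 0.03.

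- DEff = 1 + (20 - 1) × 0.05 = 1.95, and 114 × 1.95 = 222.3, rounded up to 223. The plan agrees: "assuming ρ = 0.05, would give a DEff = 1.95, or 223 women per arm". 223/20 = 11.15, stated as 11 clusters; the plan then goes to 13 and to 15.
- DEff = 1 + 19 × 0.03 = 1.57, which the plan rounds to 1.6: 114 × 1.6 = 182.4, stated as 182.
- No mean or SD is given, so 114 cannot be rebuilt. It implies a standardised difference of √(2 × (1.96 + 0.842)²/114) = 0.371.

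The clustering arithmetic reproduces to rounding. It presupposes one test at 5%.

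**2. Bounds on the error rate.** For two independent tests at 5%, P(at least one significant) = 1 - 0.95² = 9.75%. These tests are correlated. On a bivariate normal, the chance is 6.5% at correlation 0.95, 7.8% at 0.8, 8.4% at 0.7 and 9.1% at 0.5. The article gives no correlation.

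**3. Simulation with no effect.** From the article: 30 clusters of about 20 women, 15 per arm, ICC 0.03 or 0.05. Assumed: cluster-size CV 0 or 0.3, covariate ICC 0.1, and covariate R² 0 to 0.5. Models are REML random-intercept, judged against t (27-28 df) or the normal distribution (z). There were 4,000 runs per scenario; the Monte Carlo standard error near 5% is about 0.35 points.

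- Cluster t-test alone: 4.4%-5.4%.
- Cluster t-test or unadjusted mixed model, either significant: 4.5%-6.2% (t), 5.5%-6.8% (z). With equal cluster sizes the two are nearly the same test.

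Adding covariates, chance that at least one analysis is significant (t reference / z reference):

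| Assumed R² | t-test or one fixed five-covariate model | t-test, unadjusted or adjusted model | t-test or any covariate subset (1,000 runs) |
|---|---|---|---|
| 0 | 5.2-6.4% / 6.1-7.3% | 5.3-6.7% / 6.8-7.8% | not run |
| 0.1 | 6.2% / 6.9% | 6.8% / 7.9% | 10.8% / 12.9% |
| 0.2 | 7.9-8.2% / 8.6-8.9% | 8.6-8.7% / 9.9% | 13.1% / 15.5% |
| 0.3 | 7.9-9.3% / 8.9-10.0% | 8.0-9.8% / 9.6-11.0% | 19.7% / 22.9% |
| 0.5 | 8.7% / 9.8% | 9.4% / 11.0% | 23.4% / 26.8% |

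The last column has a Monte Carlo standard error of up to about 1.3 points. Covariate flexibility drives the inflation; having both a t-test and a mixed model adds little.

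**4. Cost of adjusting.** A cluster-level comparison has 30 - 2 = 28 df. Adding the cluster baseline mean and S strata leaves 28 - 1 - (S - 1) = 28 - S. The article does not give S; with four strata (assumed), 24 df remain. The two-sided 5% critical value moves from 2.048 to 2.064. With 15 clusters of 20 at ICC 0.05, the effective size is 300/1.95 = 153.8 per arm and the non-centrality for a difference of 0.371 is 0.371 × √(153.8/2) = 3.25. Power from the non-central t is 88.1% at 28 df and 87.7% at 24 df, before any gain from the baseline score.

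**The case against.** The case against has several strong parts.

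- **The text leans towards the t-test.** Significance is mentioned only there, and the move to 15 clusters per arm is justified by cluster analysis. This stands: calling the two analyses equal would overstate the text. Still, a lean is not a statement, and the article stresses that both levels will be analysed.
- **The article is condensed.** A full analysis plan, not shown, may rank the analyses and fix the covariates. This also stands, and if the only complaint were that no deciding test is named, it would be close to missing detail. What remains is that the analyses the article does state are weaker than the design allows.
- **The covariate sentence may not concern the primary outcome.** It follows the CSOM model, the child age groups and discharge duration. Reading it as a further test of the questionnaire score is an inference.

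Two stronger readings are tempting. A reader might infer that the trial's false-positive rate is about 8%-9%. The documents do not support that: they give no covariate R², no correlation between tests and no rule that either result counts as success. With t-test or one fixed adjusted model, figures of that size need R² of about 0.2 to 0.5. A reader might also infer that the mixed model is anti-conservative with 30 clusters, contrary to the article's claim. That depends on a normal reference distribution (P(|t| > 1.96) on 28 df is 6.0%), which the article never states; and for the individual-level analysis the article says only that it ought to be robust.

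**Conclusion.** The point holds in a limited form. The article attaches two analyses and an open covariate list to one primary outcome without saying which decides, and neither analysis is specified with the baseline score or, except as a possible covariate, the geographic strata.

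If any significant result counted as success, the false-positive chance would be about 5%-7% for the two analyses as specified and about 5%-10% when the t-test is paired with one fixed five-covariate model. It would be about 11%-27% with free choice among covariate subsets at R² 0.1 to 0.5. All of these depend on the assumptions above and describe what the wording permits, not what the investigators would do. With one named test the error returns to nominal. This is a worthwhile and cheap correction; it does not undermine the trial.

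**What to change.** Before follow-up scores are compared by arm, and in a dated record because data collection has already begun, name one deciding analysis of the questionnaire score. It should adjust for baseline score and the geographic allocation strata and for no other covariates. Either form would do:

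- the individual-level mixed model with a random effect for group and Kenward-Roger or Satterthwaite degrees of freedom; or
- the cluster-level comparison adjusted for cluster baseline mean and stratum, which stays closer to the article's wording.

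Label the other analysis, and any model with further covariates, as sensitivity analyses that cannot change the conclusion.

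The cost is analysis wording and a few degrees of freedom for the strata, about 0.4 points of power in the four-strata example. Sample size, data collection and conduct are unchanged.

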### Outcome measures

#### Primary outcome measure—the questionnaire

The survey instrument for women in the intervention and control groups is a questionnaire. The primary outcome measure is a 25 % difference in knowledge, attitude and practices, regarding ear disease in their children, of women in the intervention group compared to the control group. There are demographic questions such as age, number of children, maternal education, food security, usual health practices followed by questions about knowledge, attitude and practice regarding ear health, hearing, ear disease and health care seeking. The questionnaire uses already validated questions from the Demographic Health Survey (DHS) and Multiple Indicator Cluster Survey (MICS) performed recently in Nepal and is informed by a similar survey conducted in South India [32, 36, 37]. Other questions have been inspired by the *Primary Ear and Hearing Care Training Resource* and the literature on health care engagement [21]. The knowledge section asks the question ‘what do women know about ear infections in their children’, what are the local causes, treatments and complications. The attitude section queries ‘what do women think about ear infections’, is there a low level of ‘threat perception’, are there cultural barriers to seeking care, is there a perception of poor quality care or that ear infections are incurable. Finally, the practice section inquires what they do about them, whom they consult, if anyone, what would help them seek care and whether they know what care is available. The questionnaire has been pre-tested in Australia with a small adjustment made to a single question. The duration in English with educated mothers is 10 mins. Pretesting with village women on the terai (plains) did not reveal any difficulties with the questionnaire. We then undertook a formal pilot study of 20 village women in Jumla, attending INF clinics in Jumla Bazaar, to check for length, understanding and clarity. For these uneducated and illiterate women, the survey was too long and several questions incomprehensible to them. The questionnaire was edited appropriately and five questions removed from the demographic section. The new questionnaire was clear and can be completed in 10-15 mins. The questionnaires will be completed on paper in Nepali by the research assistants trained by the field team leader. Training will take place over two days in Jumla bazaar. A number of interviews will be observed by the field team leader to ensure quality control and all forms will be reviewed regularly to ensure correct completion by assistants. Baseline assessment will be performed prior to allocation into intervention and control groups to avoid bias. Group attendance and financial records are strictly kept at each meeting so it is not possible for an outsider to attend a group meeting unobserved. It is possible that there could be contamination of the control group by an intervention group member offering advice. This is not very likely as extended family mostly live side by side, meaning that grandmothers, aunties and mothers, who might share childcare and advice, are in the same group, or cluster. There are few sources of health information for these mainly illiterate women in this remote region. Followup assessment will be performed 12 months after baseline assessment. The trained research assistants performing followup assessment will be blinded to allocation.

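### The primary t-test on group mean scores does not use the pre-allocation questionnaire score: it is valid, but gives up precision and leaves chance baseline imbalance in the estimate

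*Protocol article*

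**What the plan says.** All references are to the Protocol article.

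- **Primary test** (Statistical analysis): "a summary measure, the mean score of the questionnaire, will be calculated and then the intervention and control group compared for significance with a" *t*-test on cluster-level data. The sentence gives no time point, and no change score or baseline-adjusted comparison is described anywhere.
- **Individual-level model** (same section): a mixed effects linear regression, described as adjusting for clustering.
- **Covariates** (same section): "Covariates including socioeconomic status, education, caste, geography and number of household members will be considered". The list is open and the baseline questionnaire score is not on it.
- **Use of baseline data** (same section): a profile comparing the two arms is promised. No use of the baseline score in the outcome comparison is stated.
- **Timing of the questionnaire** (Primary outcome measure): "Baseline assessment will be performed prior to allocation into intervention and control groups to avoid bias". The assessment is repeated 12 months after baseline. Study design confirms that the same women's questionnaire is used again.
- **Allocation** (Study design): 15 groups per arm, randomised with stratification by geography.

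**The concern.** A pre-allocation measurement of the primary outcome is normally among the most useful covariates a trial holds, and here it is already being collected. With only 15 groups per arm, the arms can differ noticeably in mean baseline score by chance. A plain *t*-test on follow-up group means cannot correct for this, and it leaves in the error term whatever variation between groups the baseline score would explain.

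Two things are at stake. One is the width of the interval around the primary estimate. The other is how much of an observed difference could reflect where the arms started. The precision matters more if the ICC of the questionnaire score turns out larger than planned. The article itself says that any estimate can only be approximate, and it takes its values from other outcomes, such as mortality, feeding and skilled birth attendance.

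**Working it through.** **Inputs from Sample size calculation**

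- Test, power and target: "5 % two sided Type 1 error and 80 % power to detect a 25 % difference in mean questionnaire score".
- Unclustered size: "would be 114 women in each arm".
- Mean and SD of the score: not given. Only the source is named ("Using data extracted from questions in the previous qualitative study"), so everything below is in SD units.
- Cluster size: "The cluster sizes are set at the size of the women’s groups which is around 20 women", so m = 20.
- ICC: 0.03 and 0.05 considered, 0.05 used. 15 clusters per arm.

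**Input not in the article**

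- Correlation r between baseline and 12-month group mean scores. Assumed range 0.3, 0.5, 0.7.

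**Step 1. Reproduce the plan's figures.** Design effect = 1 + (m − 1)ρ.

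- ρ = 0.05: 1 + 19 × 0.05 = 1.95; 114 × 1.95 = 222.3, rounded up to 223 as stated.
- ρ = 0.03: 1 + 19 × 0.03 = 1.57; 114 × 1.57 = 179. With the design effect rounded to 1.6, 114 × 1.6 = 182.4, which matches "assuming ρ = 0.03, would give a DEff = 1.6, or 182 women per arm".

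**Step 2. Implied target effect.** d = √[2 × (1.96 + 0.842)² / 114] = 0.371 SD. This is back-solved from 114 and is not an independent check of it.

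**Step 3. Standard error of the planned test.** Variance of a group mean = ρ + (1 − ρ)/m = 0.05 + 0.95/20 = 0.0975. SE of the difference between arms = √(2 × 0.0975/15) = 0.114 SD. Power from the noncentral t with 28 df is 88%. At ICC 0.03 it is 94%.

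**Step 4. Chance imbalance at baseline.** Taking the same variance at baseline, the between-arm difference in mean baseline score also has SE 0.114 SD, and a 95% range of ±1.96 × 0.114 = ±0.22 SD. One SE is 0.114/0.371 = 31% of the target effect. The unadjusted follow-up comparison inherits r times that imbalance:

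- r = 0.3: 0.3 × 31% ≈ 9% of the target
- r = 0.5: ≈ 15%
- r = 0.7: ≈ 22%

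**Step 5. Effect of adjusting for baseline group mean.** The variance is multiplied by (1 − r²), with 27 df.

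| | Unadjusted | r = 0.3 | r = 0.5 | r = 0.7 |
|---|---|---|---|---|
| SE multiplier √(1 − r²) | 1 | 0.954 | 0.866 | 0.714 |
| Reduction in SE | – | 5% | 13% | 29% |
| SE at ICC 0.05 (SD) | 0.114 | 0.109 | 0.099 | 0.081 |
| Power at ICC 0.05 | 88% | 91% | 95% | 99% |
| Power at ICC 0.10 | 73% | 77% | 84% | 95% |

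ICC 0.10 is an assumption, twice the planned value. The variance of a group mean is then 0.10 + 0.90/20 = 0.145 and the unadjusted SE is √(2 × 0.145/15) = 0.139 SD.

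**Step 6. Cost if baseline predicts nothing.** With r = 0 and ICC 0.05, losing one degree of freedom takes power from 88.1% to 88.0%. If stratum terms are added as well and 24 df remain, power at r = 0.5 goes from 95.2% to 95.0%.

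**The case against.** Several points on the other side stand.

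- **The test is valid.** A *t*-test on cluster summaries respects the unit of randomisation and is unbiased in expectation. A reader might infer that chance imbalance makes the planned analysis biased or wrong. It does not. The loss is in precision and in protection against the imbalance that happens to occur.
- **The trial is not underpowered by this.** On the plan's own inputs the unadjusted test has about 88% power against a planned 80%. The 73% figure needs an ICC of 0.10, above every ICC that the article cites (0.00644 to 0.04) and above the 0.05 it plans for.
- **Baseline adjustment is not ruled out.** The covariate list is open and its members are only to be considered, so the mixed model may yet include the baseline score. A reader might infer that the model adjusts for clustering alone, or that baseline data serve only the descriptive profile. The text supports neither. The final covariate set may also sit in an analysis plan not shown. This defence does not reach the *t*-test, which the article does specify and which has no place for a covariate.
- **The baseline imbalance does not pass in full into the estimate.** The 31% in Step 4 is the size of a one-SE imbalance in the baseline score. The shift in the estimate is r times that.
- **The gain depends on r.** The article expects low knowledge at baseline. A floor effect, or learning that reorders the groups, could make r small. That the baseline score is the strongest predictor is a reasonable expectation, but the article does not show it.
- **The time point is inferred.** The Abstract words the primary outcome as an increase, which could suggest change from baseline. The outcome section defines it as a difference between arms, and no change score is described.

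Stratified allocation limits imbalance in score only as far as score follows geography.

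**Conclusion.** The point holds as a matter of efficiency. The article fixes a covariate-free *t*-test for the primary comparison and does not name the baseline questionnaire score among the covariates, while collecting that score before allocation. For r from 0.3 to 0.7, adjustment narrows the standard error by 5% to 29% and removes a shift of 9% to 22% of the target effect per one-SE baseline imbalance. Power at the planned ICC rises from 88% to between 91% and 99%. If the ICC were 0.10, adjustment would bring the trial back above its 80% target at r = 0.5 or 0.7, but not at r = 0.3 (77%).

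The omission is certain for the *t*-test and open for the mixed model. The size of the benefit rests on the assumed r, on d back-solved from 114, on equal groups of 20, and on similar variance of group means at both times. The change should be made, but the trial's validity does not depend on it.

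**What to change.** Before any 12-month data are seen, specify that:

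1. the primary cluster-level analysis is a linear regression of group mean 12-month score on arm, baseline group mean score and the geographic strata used for allocation, replacing the *t*-test;
2. the mixed effects linear regression of individual 12-month scores includes the baseline score and the same strata as fixed effects, with a random intercept for group;
3. a stated rule covers women who have no baseline form.

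The article reports only that data collection has begun, and the outcome falls 12 months after baseline, so this may still be settled in time.

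Cost: a sentence or two in the plan and no new data. One degree of freedom goes to the baseline score and one to each stratum term, a negligible loss of power (Step 6). The unadjusted *t*-test can be kept as a supporting analysis.
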